### 2.11 Sample size calculation

Based on previous studies, the standard deviation (SD) of the WOMAC Pain Scale prior to surgery is approximately 17, which corresponds to an 8–9 unit difference on the scale, representing the minimum clinically perceptible improvement (Wylde et al., 2015). To detect a 0.5 SD difference in WOMAC Pain Scale scores at 3 months postoperatively, with a two-sided α = 0.05 and 80% power, a sample size of 57 patients per group is necessary. Considering a potential dropout rate of 10%, we plan to enroll a total of 128 patients, with 64 patients in each group.

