### 2.12 Statistical analysis

The normality of continuous variables will be assessed via the Shapiro-Wilk test. Normally distributed data will be presented as mean (standard deviation), whereas non-normally distributed data will be presented as median (interquartile range). For normally distributed continuous variables, independent t-tests or repeated measures ANOVA will be utilized for analysis. For non-normally distributed variables, the Mann-Whitney U test or generalized estimating equations (GEE) will be employed. Categorical data will be expressed as numbers (percentages) and analyzed via the chi-square test or Fisher’s exact test, depending on the expected frequencies. The primary outcome, the WOMAC-pain score at 3 months postoperatively, will be analyzed via a linear regression model, adjusting for baseline variables including HADS scores, PCS scores, baseline WOMAC-pain scores, sex, age, and BMI. Additionally, interactions between the treatment group and baseline scores of HADS, PCS, and WOMAC-pain will also be examined. Covariates with *p*-values <0.10 will be retained in the final model. Secondary outcomes will undergo multiple testing corrections via the Benjamini–Hochberg method, with the false discovery rate (FDR) significance level set at q < 0.05. Odds ratios (OR) and 95% confidence intervals (CI) will be reported where applicable. To ensure the robustness of our primary findings, we will conduct a sensitivity analysis using the bootstrap method. The bootstrap analysis will involve 1,000 resamples to estimate the regression coefficients and their 95% confidence intervals (CIs). This analysis will provide additional validation for the stability of the initial regression results. All results will be analyzed using a modified intention-to-treat approach, including all patients who undergo randomization and for whom relevant data are available. Statistical analyses will be conducted via SPSS software (version 25.0; IBM SPSS). A two-sided *p*-value <0.05 will be considered statistically significant unless specified otherwise for false discovery rate (FDR) corrections. Missing data will not be imputed, and no interim analyses are planned.

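### The unqualified no-imputation rule also covers baseline covariates, so randomised patients with a known 3-month WOMAC pain score can drop out of the adjusted primary regression

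*Protocol article*

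**What the plan says.** All the statements at issue are in section 2.12 of the protocol article, apart from the sample size.

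- The primary model is a linear regression, "adjusting for baseline variables including HADS scores, PCS scores, baseline WOMAC-pain scores, sex, age, and BMI".
- Beyond the main effects, "interactions between the treatment group and baseline scores of HADS, PCS, and WOMAC-pain will also be examined".
- The model is then reduced: "Covariates with *p*-values <0.10 will be retained in the final model".
- The analysis set is a modified intention-to-treat set, "including all patients who undergo randomization and for whom relevant data are available". The word relevant is not tied to the outcome alone.
- On missing values: "Missing data will not be imputed, and no interim analyses are planned". There is no exception for baseline covariates, and no missing indicator or fallback model is named.
- The only sensitivity analysis is a bootstrap of the same regression with 1,000 resamples.

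Table 1 schedules HADS, PCS and baseline WOMAC at the pre-operative visit, before allocation. The eligibility criteria in sections 2.2 and 2.3 depend on age and BMI, so those should always be known. They do not require the three questionnaires to be complete.

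Section 2.11 states that, "with a two-sided α = 0.05 and 80% power, a sample size of 57 patients per group is necessary", and adds 10% for dropout to reach 64 per group.

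**The concern.** No-imputation rules are usually written with the outcome in mind. This one is worded for all data, and it stands beside a primary model that needs three multi-item baseline questionnaires. Followed as written, it removes patients who were randomised, followed up and gave a primary outcome, only because a pre-randomisation score is blank. This is separate from loss of the outcome at 3 months.

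Two consequences follow. First, precision is lost beyond what section 2.11 allows for, because its 10% is for dropout. Second, the set of patients analysed is not fixed. The full model and the interaction models exclude anyone with a missing score. If the final model is refitted on all available records after the p <0.10 step, a patient missing only a discarded covariate comes back in. The full and final estimates could then rest on different patients. Bootstrapping the same regression cannot recover the excluded patients.

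**Working it through.** **Inputs from the documents.** 64 per group; 10% dropout; two-sided α 0.05; 80% power; a difference of 0.5 SD; SD about 17; smallest perceptible difference 8–9 units (section 2.11). Three questionnaire covariates (section 2.12).

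**Assumed input.** The rate m at which each baseline score is missing. The documents give none, so I use 0–5%.

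**Step 1: the plan's own figure.** For two means, n per group = 2(1.960 + 0.842)² / d².
- d = 0.5: 15.70 / 0.25 = 62.8, so 63 (64 by the exact t-test), not 57.
- d = 9/17 = 0.529: 15.70 / 0.2803 = 56.0, so 57 (57.0 by the exact t-test).

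The stated 57 therefore matches the upper end of the 8–9 unit range and not the 0.5 SD named. That is a separate matter, and it explains why power at 0.5 SD starts below 80% in the table. The dropout step does reproduce: 57 / 0.90 = 63.3, so 64.

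**Step 2: the margin.** 64 × 0.90 = 57.6 per arm with an outcome, against a stated need of 57. The margin is 0.6 of a patient per arm. Over both arms, 128 × 0.90 = 115.2 patients have an outcome.

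**Step 3: patients lost to missing covariates.** Two limiting patterns are considered:
- scores missing together: fraction lost = m, n per arm = 57.6(1 − m);
- scores missing independently: fraction lost = 1 − (1 − m)³, n per arm = 57.6(1 − m)³.

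For example, at m = 5% the losses are 5.0% and 1 − 0.95³ = 14.3%.

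**Step 4: power** at 0.5 SD, unadjusted two-sample t-test, two-sided 0.05.

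| m per score | Together: lost | n per arm | Power | Independent: lost | n per arm | Power |
|---|---|---|---|---|---|---|
| 0% | 0% | 57.6 | 75.8% | 0% | 57.6 | 75.8% |
| 1% | 1.0% | 57.0 | 75.4% | 3.0% | 55.9 | 74.5% |
| 2% | 2.0% | 56.4 | 75.0% | 5.9% | 54.2 | 73.2% |
| 3% | 3.0% | 55.9 | 74.5% | 8.7% | 52.6 | 71.9% |
| 5% | 5.0% | 54.7 | 73.6% | 14.3% | 49.4 | 69.1% |

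From 1% to 5%, the drop from 75.8% is 0.4 to 2.2 points if the scores go missing together, and 1.3 to 6.7 points if independently. Of the 115.2 patients with an outcome, about 1 to 6 are lost in the first case and 3 to 16 in the second.

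**Step 5: the same at 9/17 SD**, the difference that yields 57. Power starts at 80.4%. At m = 1% it is 80.0% (together) or 79.2% (independent). At m = 5% it is 78.4% or 74.0%.

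**The case against.** Several objections have force.

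- **The loss may be negligible.** The scores are taken at one pre-operative visit, and section 2.3 excludes patients whose severe sensory or speech impairments prevent assessment. Near-complete baseline data are plausible, and scores from one visit would tend to go missing together. This stands: the range must include zero, and independent missingness is the pessimistic end.
- **The power figures are for an unadjusted test.** Adjustment reduces residual variance. If the covariates explained 15% of it (an assumption), power at 0.5 SD would be 82.3% with 57.6 per arm and 79.9% with 54.2. This stands for the absolute levels; a decrement remains.
- **Handling of missing covariates belongs in an analysis plan that is not shown.** This does not remove the point. The article states a blanket rule, and a plan that filled in covariates would contradict it.
- **A missing score does not always exclude a patient from the final model.** This is correct. If that covariate fails p <0.10 and the model is refitted on available records, the patient returns. The exclusion is certain only in the full and interaction models, hence the point about an unstable analysed set.

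A reader might also infer three stronger points that the documents do not support. One is that the rule forbids scoring a questionnaire with a single unanswered item; section 2.12 says nothing about item-level scoring, and applying an instrument's own scoring rule is not normally what such a sentence addresses. Another is that adjusted and unadjusted primary results would rest on different patients; no unadjusted analysis is specifically planned for the primary outcome. The third is that the exclusions bias the comparison. The scores are scheduled before allocation, so whether they are missing cannot depend on treatment.

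**Conclusion.** The point holds as one of precision and of adherence to intention-to-treat. As written, section 2.12 drops randomised patients with an observed primary outcome from the full adjusted regression and the interaction models when HADS, PCS or baseline WOMAC pain is missing, and it lets the analysed set vary with the covariates retained.

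The size is unknown. At assumed missing rates of 0–5% per score, the loss is 0–5% of patients if the scores go missing together and 0–14% if independently, or about 0–2 and 0–7 points of power at 0.5 SD. These figures assume exactly 10% dropout, equal missing rates for the three scores and an unadjusted t-test. The shortfall of 57 per group against 0.5 SD is a different issue and adds no weight to this one. The correction is worth making because the loss is avoidable and the remedy is nearly free.

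**What to change.** Amend section 2.12 before unblinding:

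1. Limit the no-imputation rule to outcome data.
2. In the primary treatment-effect model, replace a missing baseline covariate with its mean, overall or by centre, pooled over arms and computed without using allocation or outcome.
3. State that every randomised patient with a 3-month WOMAC pain score enters the primary analysis, and that this set stays the same whichever covariates are kept.
4. Run the treatment-by-covariate interaction analyses on observed covariate values only.
5. Report the number of missing values per baseline score by arm.

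The cost is a few sentences and a few lines of code. There is a small downside: filled values slightly attenuate that covariate's own coefficient and may affect whether it passes the p <0.10 rule. Keeping the interaction analyses on observed values prevents filled values from affecting those terms.

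### The primary model is chosen by p-values from the trial's own data, and the plan does not say whether treatment-by-baseline interactions can enter it or which coefficient would then be the primary effect

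*Protocol article*

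**What the plan says.** Section 2.12 of the protocol article gives the primary analysis in three steps.

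- WOMAC pain at 3 months is analysed by linear regression, adjusted for HADS, PCS, baseline WOMAC pain, sex, age and BMI.
- In addition, "interactions between the treatment group and baseline scores of HADS, PCS, and WOMAC-pain will also be examined".
- The next sentence keeps covariates whose p-value is "<0.10 will be retained in the final model".

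The sensitivity analysis follows: "The bootstrap analysis will involve 1,000 resamples to estimate the regression coefficients and their 95% confidence intervals". The Benjamini–Hochberg correction in the same section is for secondary outcomes only. The test level is two-sided 0.05, as in section 2.11. Section 2.10 mentions a predefined statistical plan, which is not shown. Section 2.7 stratifies randomisation by centre.

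**The concern.** The trial has one confirmatory result, and the model that yields it depends on which terms happen to cross p = 0.10 in the same outcome data. A data-driven rule stated in advance does not fix the model in advance.

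Two things are at stake. First, the adjustment set is not settled, and even the baseline value of the primary outcome can be dropped. Second, the rule follows directly on the interaction sentence and speaks of one final model, so an analyst could apply it to the interactions. Nothing is said about centring or about which coefficient would then carry the primary test. With an uncentred interaction in the model, the treatment coefficient is the effect in a patient who scores 0 on that scale, not the average effect of LP5. Two analysts who both follow section 2.12 could report different primary effects with different error rates.

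**Working it through.** **Inputs from the protocol article.** Two-sided α 0.05; 57 evaluable patients per group, 64 enrolled (section 2.11); six covariates, three interactions, retention at p < 0.10 (section 2.12).

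**The plan's own figure.** With n = 2(1.960 + 0.842)²/d², a difference of 9 units on an SD of 17 (d = 0.529) gives 57 per group, and 57/0.9 gives 64 per group, 128 in all. At exactly 0.5 SD the formula gives 63, not 57. That is a separate point; here 57 per group (114 patients) is used only as the analysis size.

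**Assumptions not in the documents.** Correlation of baseline WOMAC pain with the outcome 0.2 or 0.4; correlation 0.4 among HADS, PCS and WOMAC pain; modest prognostic effects; score mean/SD ratio r from 1 to 2.5. The upper limit for WOMAC pain follows from the protocol if the SD of 17 is on the 0–50 scale of section 2.4. The variance cannot exceed m(50 − m), so m ≤ 25 + √(625 − 289) = 43.3, and r ≤ 43.3/17 = 2.55.

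**Reading A: only the six covariates are screened.** By randomisation, the treatment coefficient of a linear model without interactions targets the same average difference whichever baseline covariates stay. Simulated type I error was 4.9–6.1%.

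Chance that baseline WOMAC pain is dropped, taken on its own with 114 patients: the expected t is ρ/√(1 − ρ²) × √112, and the threshold for p < 0.10 is 1.66.
- ρ = 0.2: expected t = 2.16, dropped in about 31% of trials.
- ρ = 0.4: expected t = 4.62, dropped in about 0.2%.

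**Reading B: interactions are screened too, scores are uncentred, and the treatment main-effect coefficient is the primary test.**

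1. Chance that at least one of three null interactions passes, if independent: 1 − 0.9³ = 27.1%. In simulation with correlated scores it was about 25–28%.
2. With one interaction kept, the SE of the treatment coefficient at score 0 grows by √(1 + r²), and its correlation with the interaction estimate is r/√(1 + r²) in absolute value. A chance interaction thus pulls the treatment coefficient away from zero.
3. From the bivariate normal distribution, take c, the probability that the treatment coefficient is significant at 0.05 given that the interaction has p < 0.10. Overall type I error is then about 0.729 × 0.05 + 0.271 × c.

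| r | SE factor | correlation | c | approximate type I error | simulated, uncentred | simulated, centred |
|---|---|---|---|---|---|---|
| 1 | 1.41 | 0.71 | 25% | 10.4% | 9.5% | 5.1% |
| 1.5 | 1.80 | 0.83 | 34% | 12.9% | 11.9% | 5.8% |
| 2 | 2.24 | 0.89 | 40% | 14.4% | 12.2% | 4.8% |
| 2.5 | 2.69 | 0.93 | 43% | 15.4% | 14.5% | 5.3% |

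The simulated columns are 8,000 null trials per row, 57 per arm, the same r for all three scores, all six covariates kept and only the interactions removed backwards at p ≥ 0.10. The simulation error is about 0.2 to 0.4 percentage points. Applying the rule to all terms gave 12.1–14.8% with backward elimination and 10.6–13.2% with one-step removal, over a somewhat wider set of score ratios.

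**Reading C: as B, but with centred scores.** Type I error was about 5–6%.

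**Fixed model with all six covariates and no selection.** Type I error was 4.3–5.6% across all runs, which is nominal within simulation error.

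**The case against.** The retention rule speaks of covariates. The natural referents are the baseline variables listed just before; the interactions are introduced separately and only to be examined. On that reading the error rate barely moves and the target effect does not change. Centring is a detail that an analysis plan usually settles, and that plan is not shown. The correlations and score ratios behind the larger figures are assumptions.

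Much of this stands, and it limits the point. A reader might infer any of three stronger claims, and the documents support none of them.

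- *That the trial's type I error is about 15%.* This needs three unstated conditions together: interactions under the rule, uncentred scores, and the main-effect term as the primary test. The text allows this combination but does not prescribe it.
- *That the estimand shifts whichever way the rule is read.* With covariate screening alone it does not.
- *That the bootstrap leaves out the selection step.* Section 2.12 does not say either way.

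The objection does not remove the rule itself. It is written into the protocol for the primary outcome, so it is not a detail left for later. A plan that carries it forward would still let the data choose the adjustment set, and it would still have to say what happens when an interaction passes.

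**Conclusion.** The point holds in limited form. Section 2.12 lets the outcome data select the primary model and leaves open both the role of the interactions and the identity of the primary coefficient.

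The size depends on the reading. Covariate screening alone costs little in type I error (about 5–6%) but may discard baseline WOMAC pain, often if it is weakly prognostic and almost never at a correlation of 0.4. Uncentred interactions kept by the rule, with the main-effect term read as the primary test, give about 10–15% for score mean/SD of 1 to 2.5. Nearly all the inflation comes from the interactions, not from the covariate screening. The rule is certain from the text; the larger figure is conditional on that reading and on the assumed score distributions.

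**What to change.** Before unblinding, change the wording of section 2.12 and of any analysis plan that repeats it:

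- Delete the p < 0.10 retention rule.
- Name as the sole primary result the treatment coefficient, with its 95% confidence interval and p-value, from a linear regression without interactions. The model keeps baseline WOMAC pain, HADS, PCS, sex, age and BMI whatever their p-values, plus centre because randomisation is stratified by it.
- Test the three interactions in separate models with centred scores, labelled exploratory.
- Run the 1,000-resample bootstrap on this fixed model. The question of repeating a selection step then disappears.

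No data collection changes. With HADS as one score, the model has nine parameters (intercept, treatment, six covariates, centre), which leaves 114 − 9 = 105 residual degrees of freedom against 112 for an unadjusted comparison.

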## 3 Discussion

This randomized, double-blind, placebo-controlled trial involves 128 adult patients across two centers and aims to evaluate the preventive effects of LP5 on CPSP following knee arthroplasty. The primary objective is to assess the efficacy of LP5 in reducing CPSP, as measured by the pain subscale of the WOMAC Index 3 months postoperatively. Secondary objectives include evaluating other aspects of postoperative pain and recovery, such as WOMAC stiffness, function, and total scales; the LANSS Pain Scale; the SF-36; postoperative pain scores; VAS sleep scores; postoperative sufentanil consumption; and the need for rescue analgesia. This study will be conducted in accordance with the Consolidated Standards of Reporting Trials (CONSORT) guidelines (Moher et al., 2012). To ensure the validity of the primary outcomes, baseline variables were adjusted, and sensitivity analyses were performed to assess the robustness of the findings. These methodological considerations aim to ensure the accuracy and reliability of the results.

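### The bootstrap is said to validate stability, but nothing says the p<0.10 selection is repeated in each resample; with fixed terms it cannot test stability against that selection

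*Protocol article*

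**What the plan says.** All of this is in section 2.12 (Statistical analysis) of the protocol article.

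- The primary outcome, WOMAC pain at 3 months, "will be analyzed via a linear regression model, adjusting for baseline variables including HADS scores, PCS scores, baseline WOMAC-pain scores, sex, age, and BMI".
- In addition, "interactions between the treatment group and baseline scores of HADS, PCS, and WOMAC-pain will also be examined".
- The next sentence gives the selection rule: "Covariates with *p*-values <0.10 will be retained in the final model".
- The only sensitivity analysis named is the bootstrap: "To ensure the robustness of our primary findings, we will conduct a sensitivity analysis using the bootstrap method".
- Its content is: "The bootstrap analysis will involve 1,000 resamples to estimate the regression coefficients and their 95% confidence intervals (CIs".
- Its declared value is: "This analysis will provide additional validation for the stability of the initial regression results".

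The Discussion repeats the claim in general terms ("sensitivity analyses were performed to assess the robustness of the findings") and adds no detail. Section 2.12 does not say which model is refitted, whether selection is rerun in each resample, or whether the baseline scores are centred before interactions are formed.

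**The concern.** When the trial's own data decide which terms stay in the model, part of the uncertainty in the treatment coefficient comes from that choice. A bootstrap picks this part up only if the choice is made afresh in every resample. If the chosen terms are held fixed, each resample re-estimates the same equation on reshuffled copies of the same patients, and its interval will lie close to the primary one.

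At stake is what the report may claim. A result that owed something to the selection step could be described as validated by a check that had little chance of disagreeing. No other sensitivity analysis of the primary outcome is named.

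**Working it through.** **Which model is bootstrapped?** The wording allows three readings.

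1. The selected model is refitted with its terms fixed. This is the natural reading: one set of regression coefficients presupposes one set of terms, and nothing says how a term dropped in some resamples would be handled.
2. The model before selection is refitted, if the word initial in section 2.12 is taken literally. Selection is again not varied, and the bootstrapped model is not the final one.
3. Selection is rerun in every resample. Only this tests stability against the p<0.10 rule, and the text does not state it.

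**Inputs for sizing reading 1.** The plan gives no figure to reproduce here except the 1,000 resamples. From the documents: 57 evaluable patients per group (section 2.11), six covariates, three candidate interactions, the p<0.10 rule and a two-sided 0.05 test (section 2.12). The rest is assumed:

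- Outcome model: Y = δ·T + 0.1·HADS + 0.2·PCS + 0.3·WOMAC + e, with δ = 0 and var(e) = 0.8, so the outcome SD is about 1.
- The three scores are standard normal, with correlation 0.5 between HADS and PCS and 0.3 for the other pairs. Sex, age and BMI have no effect.
- One-pass selection at p<0.10, treatment always kept, and main effects kept with their interactions.
- Uncentred means a score mean 2 SD from zero.
- Percentile intervals, 1,500 trials per scenario, 300 resamples each.

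**Results with no treatment effect**

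| Scenario | Type I error, final model | Fixed-term bootstrap | Selection repeated | False positives still significant: fixed / repeated | Median interval width: fixed / repeated |
|---|---|---|---|---|---|
| Main effects only | 0.054 | 0.065 | 0.056 | 96% / 80% | 0.645 / 0.669 |
| Interactions, centred | 0.057 | 0.071 | 0.053 | 94% / 69% | 0.652 / 0.692 |
| Interactions, uncentred | 0.118 | 0.137 | 0.010 | 92% / 7% | 0.686 / 1.953 |
| Uncentred, skewed errors | 0.119 | 0.136 | 0.015 | 90% / 10% | 0.692 / 1.928 |

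The prespecified main-effects model gave 0.047–0.048 throughout. The simulation error of a rate near 0.05 is √(0.05×0.95/1,500) = 0.006, so 0.054 and 0.057 are barely distinguishable from nominal, while 0.118 is far from it.

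**Other assumptions.**

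- With score effects of 0.15, 0.20 and 0.25 and 1,000 resamples, the fixed-term bootstrap repeated 96% of false positives with covariates only. With uncentred interactions the final model rejected in 15.5% of trials and the fixed-term bootstrap in 16.3%, repeating 91% of false positives. Repeating the selection rejected in 1.8%, kept 11%, and gave intervals about 3.8 times as wide at the median.
- A smaller run (500 trials and 200 resamples per scenario) gave 83–93% repeated with fixed terms. With uncentred interactions, repeating the selection cut this from 90% to 15% and widened the median interval from 0.76 to 2.57.

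**Why centring decides the size.** With an uncentred interaction in the model, the treatment coefficient is the effect at a score of zero. If the score mean is 2 SD away, that coefficient is roughly the average effect minus 2 times the interaction slope per SD. The p<0.10 rule keeps an interaction when its slope happens to be large, and that same chance slope pushes the treatment coefficient away from zero. Some interaction was kept in about 25% of null trials, close to 1 − 0.9³ = 27% for three independent tests at 0.10.

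**The case against.** - **The fixed-term refit is inferred.** A reader might conclude that the protocol bootstraps only the selected model. The text does not say so, and the predefined statistical plan mentioned in section 2.10, which is not shown, may settle it. This stands as a limit. It does not remove the point, because the article attaches a claim of validated stability to a procedure which, as described, does not vary the selection under either of the first two readings.
- **A fixed-term bootstrap is not worthless.** It checks the normal-theory interval against skewed or unequal-variance errors, which is relevant for a bounded 0–50 pain score. It would therefore be wrong to infer that it shows nothing, or that it merely copies the primary result: about 4–17% of false positives were not repeated.
- **In the milder scenarios repeated selection changes little.** With main effects only or centred scores, type I error is near nominal, repeating the selection still keeps 69–80% of false positives, and intervals widen by only 4–6% (0.669/0.645 and 0.692/0.652). This stands. High overall agreement between the two analyses under the null is also weak evidence, since both mostly fail to reject.
- **Pooling can mix two parameters.** With uncentred scores, resamples that keep an interaction estimate the effect at score zero, and the others estimate the average effect. Part of the widening, and of the rejection rates of 0.010–0.018, reflects this mixture. This stands, and is why the remedy needs centring.
- **The number of resamples is a matter of preference.** The Monte Carlo error of a percentile limit at 1,000 resamples is √(0.025×0.975/1,000)/φ(1.96), about 0.08 standard errors. It changes no primary decision and is not part of this point.
- **The root is the selection rule.** Fixing the covariates in advance would remove the problem. That is one of the two remedies below.

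**Conclusion.** The point holds in limited form. Section 2.12 does not state that selection is repeated. If it is not, the bootstrap cannot validate stability against the p<0.10 selection, and it left roughly 83–96% of false positives significant in simulation. What it can support is the normal-theory interval against departures from normal, equal-variance errors.

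The practical size depends on something the article leaves open. If treatment interactions with uncentred scores can enter the final model, type I error was about 0.12–0.16 and the fixed-term bootstrap would mostly endorse the excess. With main effects only or centred scores it was about 0.05–0.06, and little is lost. These figures rest on assumed correlations, covariate effects, score coding and one-pass selection, none of which the documents give.

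A reader might infer that the trial's false-positive rate is certainly inflated. The documents do not support that: they say interactions will be examined and covariates retained, without saying that interactions fall under the retention rule or that scores are left uncentred.

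**What to change.** Choose one of these in section 2.12 or the statistical plan.

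1. Prespecify the covariates and drop the p<0.10 rule. Bootstrap that fixed model and describe the result only as a check of distributional assumptions.
2. Keep the rule, but state that every resample reruns the whole selection. Centre the baseline scores so that the treatment coefficient keeps one meaning. Report the percentile interval for the treatment effect and how often each covariate and interaction is retained.

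If neither is adopted, remove the claim that the bootstrap validates the stability of the results.

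The cost is a sentence or two and, for the second option, a short script. The second option may give a wider, less flattering bootstrap interval: about 4–6% wider in the milder scenarios above, and possibly more if selection proves unstable in the trial data.
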